| Protocol date             | 04-02-2025                                                                                                                                                                                                                                                                                                                |
| Study initiation          | 01-12-2020                                                                                                                                                                                                                                                                                                                |
| Study duration            | Minimum of 10 years                                                                                                                                                                                                                                                                                                       |
| Sample size               | All patients diagnosed with moderate-severe mitral regurgitation by echocardiography at participating centres will be included in the study. There will be no predefined stopping point for patient inclusion. These patients will be registered at four participating hospitals and followed for a period of five years. |
| Principal Investigators   | [name]                                                                                                                                                                                                                                                                                                                    |
| Coordinating Investigator | MW                                                                                                                                                                                                                                                                                                                        |
| Steering committee        | [name]                                                                                                                                                                                                                                                                                                           |
| Study Centres             | Maastricht UMC+, Maastricht, The Netherlands
Zuyderland MC, Sittard and Heerlen, The Netherlands
VieCuri MC, Venlo, The Netherlands
Laurentius Hospital, Roermond, The Netherlands                                                                                                                               |
| Study Hypothesis          | Through the repeated quantitative evaluation of patients with moderate-severe mitral valve regurgitation, we can achieve a more comprehensive                                                                                                                                                                             |

|                                |                                                                                                                                                                                                                                                                                                                                                                                                                                                                                     |
|--------------------------------|-------------------------------------------------------------------------------------------------------------------------------------------------------------------------------------------------------------------------------------------------------------------------------------------------------------------------------------------------------------------------------------------------------------------------------------------------------------------------------------|
|                                | characterization of disease progression, thereby enabling the individualized adjustment of personalised treatment strategies.                                                                                                                                                                                                                                                                                                                                                       |
| Study Design            | An observational prospective database will be used. No randomization will take place in this study.                                                                                                                                                                                                                                                                                                                                                                                 |
| Study population        | All patients with moderate-severe mitral valve regurgitation, as determined by echocardiography, from the designated participating centres.                                                                                                                                                                                                                                                                                                                                         |
| Objectives              | The co-primary endpoints are all-cause mortality and heart failure hospitalisations over a five-year follow-up period. Secondary objectives are to describe management strategies, evaluate mitral regurgitation progression and cardiac remodelling, investigate associations between baseline clinical and echocardiographic characteristics and long-term outcomes, identify predictors of treatment success, and assess longitudinal changes in health-related quality of life. |
| Inclusion criteria      | All patients aged 18 years or older with moderate-severe MR as determined by echocardiography.                                                                                                                                                                                                                                                                                                                                                                                      |
| Exclusion criteria      | Patients who object to participation in the registry.                                                                                                                                                                                                                                                                                                                                                                                                                               |
| Follow-up               | Five years of follow-up, with an annual collection of patient characteristics, echocardiographic parameters, and the Short Form 36 Health Survey Questionnaire.                                                                                                                                                                                                                                                                                                                     |
| GCP and data protection | These studies will be performed in compliance with good clinical practices guidelines, and data will be handled in accordance with the European General Data Protection Regulation.                                                                                                                                                                                                                                                                                                 |
| Confidentiality status  | The information contained herein is confidential and the proprietary property of the principal investigators.                                                                                                                                                                                                                                                                                                                                                                       |

| MUMC+ | Maastricht University Medical Centre+               |
| NYHA  | New York Heart Association                          |
| PISA  | Proximal isovelocity surface area                   |
| SF-36 | 36-Item Short Form Survey                           |
| sPAP  | Systolic pulmonary artery pressure                  |
| SMILE | Significant Mitral Insufficiency Limburg Evaluation |
| WGBO  | Dutch Civil Code: Medical Treatment Contracts Act   |
| WMO   | Medical Research Involving Human Subjects Act       |

## **1 Introduction and rationale**

Mitral regurgitation (MR) affects more than 10% of individuals aged 75 years and older and is associated with adverse cardiovascular outcomes, including heart failure, increased hospitalizations, and mortality (1-3). Despite its prevalence, MR is often undertreated, leading to progressive disease, adverse cardiac remodelling, and diminished quality of life (HRQoL) (1, 4, 5). While advancements in diagnostic and therapeutic technologies have improved outcomes, optimal management strategies, particularly in asymptomatic patients, remain unclear due to discrepancies in guidelines and a lack of robust data (6-8). However, timely intervention has been shown to improve outcomes significantly (6).

The multicentre prospective Significant Mitral Insufficiency Limburg Evaluation (SMILE) registry aims to evaluate long-term outcomes in patients with moderate-severe MR in routine clinical practice, and to determine clinical and echocardiographic predictors of MR progression and treatment success. Through a multidisciplinary approach, the registry aims to align the progression of mitral valve disease and care pathways with individual patient needs, optimize treatment strategies, and enhance long-term outcomes, including survival and HRQoL.

## **2 Objectives**

### **2.1 Primary objective**

To evaluate the co-primary clinical endpoints during a five-year follow-up:

- all-cause mortality
- heart failure hospitalisations

### **2.2 Secondary objectives**

- To describe contemporary management strategies in patients with moderate-severe MR.
- To evaluate associations between baseline patient characteristics and long-term clinical outcomes.
- To evaluate MR disease progression over time.
- To identify key predictors associated with treatment success.
- To assess longitudinal changes in HRQoL.

## **3 Study design**

### **3.1 Proposed timeline of trial**

This study aims to create an ongoing, continuous database that will capture all patients with moderate-severe MR in Limburg, allowing for comprehensive long-term data collection and monitoring of this population.

## **4 Study population**

### **4.1 Population**

All patients with moderate-severe MR, as determined by echocardiography, from the designated participating centres (Maastricht University Medical Centre+ (MUMC+), Maastricht; VieCuri Medical Centre, Venlo; Laurentius Hospital, Roermond; Zuyderland Medical Centre, Heerlen, and Sittard/Geleen).

### **4.2 Inclusion Criteria**

All patients aged 18 years and older with moderate-severe MR as determined by echocardiography.

### **4.3 Exclusion Criteria**

Patients who object to participation in the registry.

### **4.4 Sample size**

There will be no predefined endpoint for patient inclusion. The register strives to enrol all patients who meet the criteria for moderate-severe MR, as determined by echocardiography, from the designated participating centres. These patients will be registered at the four participating hospitals and followed up for a period of five years.

#### 4.5 Study flow diagram

[figure not shown]

## **5 Methods**

### **5.1 Study parameters/endpoints**

The study included key patient characteristics, such as age, gender, height, weight, and New York Heart Association (NYHA) class. Echocardiographic parameters included left ventricular ejection fraction (LVEF), mitral valve aetiology, MR severity, left atrial volume index (LAVi), effective regurgitant orifice area (EROA), regurgitant volume, and systolic pulmonary artery pressure (sPAP). Follow-up data, including all-cause mortality and heart failure hospitalisations, are collected during annual follow-up and verified through medical records, with dates recorded. The registry additionally captures mitral valve interventions and other cardiac procedures that may influence outcomes. HRQoL is assessed at baseline and annually using the 36-Item Short Form Survey (SF-36). Additional variables, including detailed echocardiographic measurements (e.g., vena contracta, PISA radius, LVEDD, LVESD) and comprehensive follow-up variables (e.g., cardiac interventions), are presented in the appendix.

### **5.2 Randomisation, blinding and treatment allocation**

There is no randomization involved. Participants will continue to receive standard care, and no additional interventions or investigations will be applied.

### **5.3 Study procedures**

The database does not require any changes to the participants' usual care, and they will not undergo any procedures other than echocardiographic evaluation and follow-up. Follow-up will take place through regular outpatient visits at the referring hospital. Participating patients will be asked to complete an annual SF-36 questionnaire, with follow-up occurring once yearly for five years. Completing the SF-36 questionnaire will take approximately 15 minutes. Additionally, data from patient records will be collected for five years.

### **5.4 Schedule of assessment**

No additional procedures are planned. All assessments will follow the standard care protocol.

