### **11.2 Disease-specific endpoints (Secondary)**

MR disease progression will be assessed using longitudinal echocardiographic evaluations performed during routine clinical care. MR severity will be assessed according to guideline-recommended criteria at the time of analysis. MR progression will be defined as an increase of at least one MR grade compared with baseline.

In addition, left ventricular (LV) and left atrial (LA) remodelling will be assessed longitudinally using echocardiographic parameters. LV remodelling will be evaluated using LV end-diastolic diameter (LVEDD) and left ventricular ejection fraction (LVEF), while LA remodelling will be evaluated using LA volume index (LAVi). For clinical interpretability, remodelling severity will additionally be categorised based on guideline-recommended cut-off values at the time of assessment. For patients already in the most severe category at baseline, progression will be defined as a relative change of  $\geq 10\%$  from baseline.

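### Progression and treatment success rest on routine-care echoes whose indication is not recorded, so state-dependent echo timing could bias these secondary analyses and the planned complete-case check would not show it

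*Protocol*

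**What the plan says.** The follow-up row of the protocol synopsis plans "Five years of follow-up, with an annual collection of patient characteristics, echocardiographic parameters, and the Short Form 36 Health Survey Questionnaire". Section 11.4 derives treatment success from annual assessments. After intervention, MR must be grade 2 or lower. Under conservative management, MR must not have worsened. Both definitions also have a symptom or quality-of-life component.

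No echo is mandated. Section 5.2 says that "no additional interventions or investigations will be applied", section 5.4 says "No additional procedures are planned. All assessments will follow the standard care protocol", and section 11.2 says that "MR disease progression will be assessed using longitudinal echocardiographic evaluations performed during routine clinical care". Section 5.3 is looser, stating that "they will not undergo any procedures other than echocardiographic evaluation and follow-up". Section 10 lists echocardiography and yearly visits among routine evaluations and attaches the yearly interval to the visits.

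The progression endpoint in section 11.2 is simple: "MR progression will be defined as an increase of at least one MR grade compared with baseline".

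Section 7.1 does not impute missing data. It uses all available data for the primary analyses and complete-case cohorts for sensitivity. The appendix lists the date of each echo but has no field for its indication.

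**The concern.** When routine care decides who has an echo and when, the decision can depend on how the patient is doing. New symptoms, an admission or work-up for an intervention may each lead to an echo, while a stable patient may have none in a given year. The patients with a follow-up MR grade are then not a neutral sample of the cohort.

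The analyses are exposed to different degrees:

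- **Progression proportion.** It is computed among patients with a later grade and has no protection against selective grading.
- **Responder logistic model.** A conservatively managed patient with no follow-up echo cannot be classified on MR worsening and, without imputation, drops out. After intervention, success is dated to the first qualifying assessment, so it also depends on how often MR is graded.
- **Mixed models.** They tolerate timing that depends on data already observed and modelled, but not timing driven by factors outside the model, such as a symptom arising between visits.

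MR progression and predictors of treatment success are stated aims of the registry (sections 1 and 2.2), so the descriptive rates and the predictor estimates are both at stake.

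**Working it through.** The protocol gives no progression rate, echo completion rate or sample size, so there is no planned figure to reproduce. The calculation below shows only how far the observed rate could move.

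**Inputs, all assumed:**

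- p = true proportion progressing within a year
- a = probability of an echo given progression, set at 0.90
- b = probability of an echo given no progression, varied from 0.90 to 0.30

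**Formula.** Observed progression among echoed patients = p·a / (p·a + (1 − p)·b).

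**With p = 0.10**, p·a = 0.10 × 0.90 = 0.09:

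| b | (1 − p)·b | Observed rate | Ratio to true rate |
|---|---|---|---|
| 0.90 | 0.81 | 0.09 / 0.90 = 10.0% | 1.00 |
| 0.80 | 0.72 | 0.09 / 0.81 = 11.1% | 1.11 |
| 0.70 | 0.63 | 0.09 / 0.72 = 12.5% | 1.25 |
| 0.50 | 0.45 | 0.09 / 0.54 = 16.7% | 1.67 |
| 0.30 | 0.27 | 0.09 / 0.36 = 25.0% | 2.50 |

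**Other true rates**, same range of b:

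- p = 0.20: from 0.18 / 0.90 = 20.0% to 0.18 / 0.42 = 42.9%
- p = 0.30: from 0.27 / 0.90 = 30.0% to 0.27 / 0.48 = 56.3%

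The bias is zero when a = b. It would reverse if stable patients were echoed more often than those who progress.

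**Five-year view.** Suppose that a stable patient has a 30% chance of an echo each year, independently between years. The chance of at least one in five years is 1 − 0.70^5 = 0.832. If every progressor is echoed at some point and true five-year progression is 10%, the observed proportion is 0.10 / (0.10 + 0.90 × 0.832) = 0.10 / 0.849 = 11.8%, or 1.18 times the truth. The one-year upper figure of 25% therefore does not carry over to cumulative five-year progression. Yearly rates and annual responder status remain nearer the one-year case.

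**Why the complete-case analysis does not help.** A patient enters the complete-case cohort by having the required echoes, which is the process in question. Agreement between the two analyses would give no reassurance, and a difference could not be attributed to echo timing.

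**The case against.** The strongest reply is that the passages fit together. The synopsis speaks of collecting echo parameters yearly, which for a registry means data capture. The sentence in section 5.3 that names echocardiographic evaluation opens by saying that usual care is unchanged. Read whole, the plan is routine echoes abstracted once a year. This largely stands: section 5.3 is loosely worded, and a reader who infers a flat contradiction goes further than the text.

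A reader might also infer that progression will be measured mainly in patients whose condition prompted an echo. No passage says so, and none gives the share echoed each year. Section 10 leaves room for scheduled echoes within routine care, in which case the bias could be nil. State-dependent timing is a risk, not an established fact.

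Three further limits stand. The definitions do not require a grade every year: section 11.2 compares with baseline at no fixed time, and after intervention one qualifying assessment is enough. The mixed models are not biased as such, only when timing depends on factors outside the model. Prompted echoes are not wholly unidentifiable, because echo dates, heart failure admission dates, interventions and NYHA class allow an imperfect reconstruction.

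Finally, visit windows and extra sensitivity analyses commonly belong in a statistical analysis plan, which is not shown here, so their absence is not the criticism. What remains is that section 7.1 fixes a sensitivity analysis that cannot address this risk, and that no later plan can use an indication that was never collected.

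**Conclusion.** The point holds as a conditional risk. Annual echo data and annual responder status depend on echoes whose timing is left to routine care and whose reason is not recorded. If timing follows clinical state, the progression proportion and the responder model may be biased, as may the mixed models where timing depends on unmodelled factors. The planned complete-case analysis cannot reveal this.

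The size cannot be settled from the protocol. With 10% true one-year progression and 90% of progressors echoed, both assumed, the observed rate lies between 10% and 25% as the share of stable patients echoed falls from 90% to 30%. The effect on cumulative five-year progression is smaller.

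Both co-primary endpoints, all-cause mortality and heart failure hospitalisation, are ascertained without echo and are untouched. This is an inexpensive improvement to secondary analyses, not a flaw in the main ones.

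**What to change.** 1. **Sections 5.3 and 5.4.** State that follow-up echoes are routine-care echoes abstracted yearly, and align the synopsis and section 11.4 with that.
2. **Main analysis.** Keep all echoes at their actual dates and treat MR progression as interval-censored between echoes. This handles the unknown date of progression but does not by itself correct for state-dependent timing, hence step 3.
3. **Section 7.1.** Alongside the complete-case check, add a sensitivity analysis with inverse-intensity-of-visit weights built from recorded NYHA class, heart failure admission dates and interventions. It corrects only for what is recorded.
4. **Reporting.** Give the share of living patients with an echo in each annual window, by aetiology and management strategy. This shows whether the cohort lies near the no-bias end of the range.
5. **Data collection.** Prospectively add one eCRF field per echo: planned or prompted. Use a surveillance-only analysis as a sensitivity analysis and not as the main one. A patient whose progression is found on a prompted echo, and who then has an intervention or dies, might never contribute a progressed surveillance echo, so that analysis can understate progression.

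None of this adds an investigation or changes care. The cost is modest data entry and analysis time. The indication may be unavailable for echoes already collected since the registry began in December 2020, so steps 3 and 4 must carry the earlier years.
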